## Abstract

**Introduction:**

Enteric fever, primarily caused by *Salmonella enterica* Typhi and *Salmonella enterica* Paratyphi A (SPA), is endemic mainly in South Asia, disproportionately affecting school-age children. Although typhoid conjugate vaccines (TCVs) are effective and implemented in many countries, no licensed vaccine exists against paratyphoid A. Bivalent vaccines targeting both S. Typhi and SPA may address this gap. Although field efficacy trials are not considered feasible, controlled human infection models (CHIMs) offer an alternative pathway for evaluating vaccine efficacy. This will be the first efficacy study of a bivalent vaccine against typhoid and paratyphoid A using a paratyphoid CHIM.

**Methods and analysis:**

This is a phase II multicentre, double-blind, randomised controlled trial assessing the efficacy and immunogenicity of a bivalent conjugate vaccine candidate, Serum Institute of India Typhoid Conjugate Vaccine (Bivalent) (SII-TCV(B)), against SPA using a CHIM in healthy UK adults aged 18–55 years. A total of 192 participants will be randomised 1:1 to receive either SII-TCV(B) or a licensed Vi-polysaccharide typhoid vaccine (Vi-PS). All participants will be orally challenged with S. Paratyphi A (strain NVGH308) 28 days postvaccination. Participants will be monitored closely for 14 days and treated at 14 days postchallenge or promptly on diagnosis, according to prespecified criteria. The primary objective is to evaluate vaccine efficacy of SII-TCV(B) against paratyphoid infection using a CHIM. The coprimary immunogenicity objective is to assess non-inferiority of the typhoid IgG response compared with a licensed Vi-PS control.

**Ethics and dissemination:**

The study has received ethical approval from the Berkshire Research Ethics Committee (24/SC/0309) and regulatory approval from the UK Medicines and Healthcare products Regulatory Agency. Results will be disseminated via peer-reviewed publications and scientific meetings.

**Trial registration number:**

ISRCTN65855590.

STRENGTHS AND LIMITATIONS OF THIS STUDYThe multicentre, randomised, double-blind, controlled design of the study, with stratified allocation, will provide high-quality data.The use of a controlled human infection model will enable efficacy assessment of the first bivalent typhoid-paratyphoid A vaccine candidate, since field trials are not considered feasible due to the high cost and large sample size required.Rigorous screening procedures, including gallbladder ultrasound, prevention of chronic faecal carriage of *Salmonella* enterica Paratyphi A and enforced infection control precautions, ensure safety of the participants and their close contacts.A centralised administration of challenge associated with fully validated centralised immunogenicity assays (including anti-Vi and anti-LPS IgG and IgA for primary and secondary objectives) will provide consistent endpoints.The sample size was calculated to provide 90% power to detect a vaccine efficacy higher than 30% and to demonstrate non-inferiority of Serum Institute of India–Typhoid Conjugate Vaccine(B) compared with a plain polysaccharide typhoid vaccine as control.

## Introduction

 The lack of a licensed vaccine against *Salmonella* enterica Paratyphi A (SPA) is a major gap in enteric fever prevention. Although typhoid fever accounts for the majority of enteric fever cases globally, paratyphoid fever is responsible for over 20% of all cases of enteric fever.^1^ SPA is estimated to be responsible for up to 99% of cases of paratyphoid fever^2 3^ and poses a significant and growing public health threat in low-income and middle-income countries where safe water and sanitation infrastructure are inadequate. With a global annual burden of 14 000 deaths and over 1 million disability-adjusted life years (DALYs) in 2021^4^ attributed to paratyphoid fever alone, it affects predominantly school-age children in South Asia. The epidemiology of paratyphoid disease is evolving, including escalating antimicrobial resistance^5^,^7^ and an increasing proportion of enteric fever cases,^8^ highlighting the need for urgent preventive measures. Although the provision of safe water, sanitation and hygiene measures is urgently needed to prevent enteric fever,^9^,^12^ these take time and financial investment. Vaccines are, therefore, a useful intervention to reduce the paratyphoid fever burden in the meantime.

Historical inactivated whole-cell vaccines against typhoid and paratyphoid A and B were available by the beginning of the 20th century. However, their efficacy against paratyphoid was unclear, and they were discontinued due to unacceptable tolerability.^13 14^ Since then, the development of vaccines against typhoid fever has been prioritised over the investigation of vaccines against paratyphoid fever. Recent efforts to investigate paratyphoid vaccines have concentrated on oral live attenuated^15^ or inactivated vaccines based on O2:LPS antigen,^16^,^18^ and combined vaccines with typhoid and even with other Salmonella enterica serovars are in development.^19^,^23^ However, advancing their development has been challenging due to a lack of an appropriate preclinical animal challenge models (S. Paratyphi A is a human-restricted pathogen) and absence of immunological correlates of protection. Field efficacy trials are considered unaffordable and logistically demanding, requiring as many as over one hundred thousand volunteers, therefore considered infeasible.^24 25^

Licensed vaccines against typhoid fever are available: the monovalent conjugate Vi-polysaccharide vaccines against typhoid (typhoid conjugate vaccines, TCVs) are recommended by WHO since 2017,^26^ considered cost-effective in high-incidence countries^27 28^ and being incorporated into routine immunisation schedules of endemic countries.^29^ TCVs have an efficacy above 80%,^30^,^32^ even in outbreak contexts,^33^ contributing to significant disease prevention since they were administered to over 64 million children.^34^ Although TCVs effectively protect against typhoid fever, there is a gap in the enteric fever prevention, since TCVs do not address the paratyphoid burden and may contribute to a serovar replacement.^35^,^39^

To tackle the enteric fever burden more comprehensively, a vaccine that would extend coverage against paratyphoid as well as typhoid would be desirable for stakeholders.^22 24^ Combined vaccines have multiple advantages over monovalent vaccines. They reduce costs and logistical burdens by reducing materials (eg, syringes, needles), storage requirements and healthcare visits. Additionally, combining typhoid and paratyphoid A vaccines is practical, given their overlapping demographic and geographical distribution in South and Southeast Asia.^40^ Polysaccharide-protein conjugate vaccines have practical advantages over other platforms, including high efficacy even in children as young as 6 months of age due to generation of a T-cell dependent immune response with B-cell memory, alongside low cost and few cold chain requirements.^41^

Licensing new TCVs can be achieved through demonstration of non-inferiority in immunogenicity studies, comparing with licensed Vi-polysaccharide typhoid vaccine (Vi-PS) or other licensed TCVs.^24^ This pathway is not applicable for paratyphoid vaccine candidates. Controlled human infection models (CHIM) provide a cost-efficient and time-efficient alternative to test vaccine efficacy (VE).^24^ The Oxford Vaccine Group (OVG) has established a typhoid^42^ and a paratyphoid CHIM.^43^ The successful experience testing a TCV in this experimental setting^44^ showed the potential of CHIM as a robust tool for testing enteric fever vaccine candidates, providing data towards WHO prequalification of the vaccine.^45 46^ In 2022, the WHO’s Product Development for Vaccines Advisory Committee (PDVAC) suggested CHIMs could be used to accelerate testing and consequent licensure of bivalent typhoid and paratyphoid A vaccines,^24^ and our group has recently evaluated a monovalent paratyphoid VE using CHIM,^47^ results expected in 2025.

This trial will be the first to test a bivalent conjugate vaccine against both typhoidal serovars causing enteric fever using a SPA CHIM. Serum Institute of India Typhoid Conjugate Vaccine (Bivalent) (SII-TCV(B)) was proven safe in a phase I trial^18^ and, if proven efficacious, this vaccine could achieve expedited licensure and prequalification,^24^ allowing comprehensive deployment to tackle the dual burden of typhoid and paratyphoid fever, a significant step forward in global health.

## Study aims and objectives

This study aims to assess the efficacy of one dose of the bivalent conjugate vaccine candidate SII-TCV(B) against SPA in a CHIM, and to demonstrate non-inferiority of the immune response to the S. Typhi component compared with a UK-licensed typhoid vaccine. Secondary and exploratory objectives include characterisation of immune response to the vaccine and to the challenge, assessment of vaccine safety, and investigation of correlates of protection against SPA. Table 1 lists primary and secondary objectives and outcomes, with a complete list found in more detail in the online supplemental table S1.

**Table 1 T1:** Primary and secondary objectives and outcomes of the BiVISTA study

Study objectives	Outcome measures
Primary objectives	
To evaluate the efficacy of SII-TCV(B) against SPA compared with a licensed Vi polysaccharide vaccine in a healthy adult paratyphoid A challenge model	Proportion of participants developing S. Paratyphi A infection within 14 days following challenge, according to pre-specified diagnostic criteria
To evaluate the non-inferiority of the immune response to the *Salmonella* Typhi component of SII-TCV(B) compared with the licensed Vi Polysaccharide vaccine	Geometric mean concentration (GMC) of S. Typhi Vi antigen-specific IgG at day 28 following vaccination
Secondary objectives	
To evaluate the safety and tolerability of SII-TCV(B) compared with a licensed Vi polysaccharide vaccine	Occurrence of: local solicited events in 7 days following vaccination systemic solicited events in 7 days following vaccination unsolicited events in 28 days following vaccination serious adverse events following vaccination throughout study participation
To evaluate the immunogenicity of SII-TCV(B) compared with a licensed Vi polysaccharide vaccine	Quantification of S. Paratyphi A antigen-specific antibodies at 28 days following vaccination: GMCs, geometric mean fold rise (GMFR) and seroconversion (fourfold rise to prevaccination) for anti-LPS IgG, IgA and IgM and SBA titres Quantification of S. Typhi antigen-specific antibodies at 28 days following vaccination: GMCs, GMFR and seroconversion (four-fold rise to prevaccination) for anti-Vi IgG and IgA

BiVISTA, Bivalent Vaccination against *Salmonella* Typhi and SPA; SBA, serum bactericidal assay; SII-TCV(B), Serum Institute of India Typhoid Conjugate Vaccine (Bivalent); TCV, typhoid conjugate vaccine.

## Methods

### Study design

This manuscript is written according to protocol version 2.1, dated 29 January 2025. Two independent researchers and members of the DSMC (Data and Safety Monitoring Committee) reviewed and contributed to the protocol prior to finalisation.

The study is a multicentre, double-blinded, randomised, controlled, outpatient trial of the vaccine candidate SII-TCV(B) against typhoid and paratyphoid A, using a CHIM of healthy adult volunteers experimentally infected with SPA. The planned study period is from October 2024 until September 2027, with the first participant recruited in March 2025.

In total, 192 individuals will be randomised to receive a single intramuscular dose of either SII-TCV(B) or a UK-licensed polysaccharide typhoid vaccine (Vi-PS), Typhim Vi. 28 days after the blinded vaccination, all participants will be orally challenged with a single dose of 1–5×10^3^ CFU (colony-forming units) SPA strain NVGH308. The dose was established in a previous study conducted at the OVG to achieve a 55%–75% attack rate (proportion of participants diagnosed with paratyphoid A infection by prespecified endpoint criteria, see table 2) using the same strain.^43^ This dose was later used in two subsequent SPA CHIM studies at the OVG with attack rate within the same range.^47 48^ All participants will be monitored daily after the challenge, and they will all be treated with antibiotics either at the time they reach the diagnosis criteria or at 14 days, whichever will be sooner.

**Table 2 T2:** Summary of inclusion and exclusion criteria (full list, including temporary exclusion, is described in online supplemental material)

Summary of inclusion and exclusion criteria	
Inclusion criteria	Willing and able to give informed consent. Healthy adults aged between 18 and 55 years. Available for all required appointments at the study centre. Ability to comply with all study requirements, including adherence to good personal hygiene and infection control precautions. Agree to allow the study team to access their medical history and immunisation records. Agree to allow their GP (and/or consultant if appropriate) and National Public Health Agency to be notified of participation in the study. Agree to give their close household contacts written information about their involvement in the study, offering them voluntary screening for S. Paratyphi A carriage. Agree to be contactable by mobile phone and to have a 24-hour contact person to allow the study team to speak to them during the 4 weeks postchallenge. Agree to avoid antipyretic/anti-inflammatory medications during the challenge phase until antibiotic treatment. Agree to be registered onto The Over-Volunteering Prevention System.
Exclusion criteria	History of significant organ/system disease that could interfere with study conduct or completion, in the opinion of the study team. Including but not limited to the following: history of any calculi (urinary or biliary), any gastro-intestinal condition leading to chronic diarrhoea or chronic constipation or use of regular medications for gastrointestinal tract, known or suspected drug or alcohol abuse or history of severe or psychotic mental health condition, or history of cancer. Any impairment of immune function, for example, IgA deficiency, auto-immune disease, HIV infection, use of immunosuppressive drugs or radiotherapy. HLA-B27 positive. Moderate or severe depression or anxiety as classified by the Hospital Anxiety and Depression Score at screening or challenge that is deemed clinically significant. Weight less than 50 kg. Presence of implants or prosthetic material. Taking long-term medication that may affect symptom reporting or interpretation of the study results or that may interact with antibiotics used for treatment of paratyphoid A (particularly drugs that could prolong corrected QT interval). Contraindication to antibiotics used in the study. Family history of aneurysmal disease. Participants who are pregnant, lactating or who are unwilling to ensure effective contraception until faecal clearance. Close house contact or occupation involving direct contact with young children or with anyone immunosuppressed (including pregnant individuals), unless willing to be moved to avoid any contact with these individuals. Anyone in Commercial food handling (involving preparing or serving unwrapped foods not subjected to further heating). Detection of any clinically significant abnormal results from screening investigations. Having been resident in an enteric fever endemic country for 6 months or more. Previous confirmed or suspected typhoid or paratyphoid infection or participation in previous enteric fever challenge studies (with ingestion of challenge agent). Receipt of any typhoid vaccination at any time. Prolonged corrected QT interval (>450 ms) or significant clinical abnormality on ECG. Presence of gallbladder abnormalities (eg, calculi, polyps) on ultrasound. Significant blood donation or planned blood donation prior to study vaccination. Evidence of HIV, hepatitis B or hepatitis C infection. Any other medical or social condition that may affect participation in the study.

GP, general practitioner.

The study is sponsored by the University of Oxford and will be conducted in 13 study centres (listed in the online supplemental material). All parent sites are equipped for safe participant review and adequate sample processing. Participants will be recruited, vaccinated and followed up at their parent site. Challenge agent administration will be centralised and conducted under predefined standard operating procedures. A study design diagram is presented in figure 1. Participants will be reimbursed for their time, travel and inconvenience.

**Figure 1 F1:**
[figure not shown]
Study design and visit timeline. After screening, participants are vaccinated with intramuscular test or comparator vaccine at D-28, with follow-up visits at D-21 and D-14. All participants undergo oral *Salmonella* enterica Paratyphi A challenge at D0 with daily visits until D14. Antibiotic treatment starts at the time of diagnosis or at day 14 for those who were not diagnosed, whichever is sooner. Participants have a phone follow-up visit at D21 and an in-person follow-up at D28. Electronic diaries collect data from D-28 to D28. After completing treatment, all participants are required to bring three stool samples to ensure bacterial clearance. The last follow-up visits are at D90 and D180. D, day; SII-TCV(B), Serum Institute of India Typhoid Conjugate Vaccine (Bivalent)

Infection prevention and control measures will be in place at the research facilities and taught to participants to practise at home to avoid spread of the challenge strain.

### Recruitment and eligibility

Recruitment advertisements will use approved text and will be widely distributed.

Healthy adult volunteers aged 18–55 years will be directed to read the Participant Information Sheet to undergo a screening process, summarised in online supplemental figure S1, when they will sign an informed consent form, which is available as online supplemental material. Inclusion and exclusion criteria are summarised in table 2 (full list is in online supplemental material). When found eligible, participants will be invited to trial vaccination. On the vaccination day and on the challenge day, temporary exclusion criteria (listed in online supplemental material) will also be applied. The trial management group will actively monitor the representativeness of our trial population.

### Trial procedures

Vaccination will occur at day 28 visit. Challenge day will mark day 0, followed by 14 daily visits. In-person follow-up time points will be at 7, 14 and 28 days after vaccination and 28, 90 and 180 days after challenge, with a phone follow-up on day 21 postchallenge. The visit schedule is detailed in figure 1.

Since infection caused by SPA is notifiable, UK Public Health authorities will be informed about the conduct of the trial and will be notified of challenged individuals, for which participants will be specifically consented.

#### Randomisation

Participants will be randomised in a 1:1 ratio to receive a single intra-muscular dose of SII-TCV(B) or a Vi-PS (Typhim Vi). A randomisation list, generated by an OVG statistician using random block sizes (2 and 4), will be used to ensure equal target size in both arms. The randomisation will be stratified by parent site and uploaded to a web-based system (Research Electronic Data Capture, REDCap) that automates the allocation.

Unblinded clinical staff will run the randomisation on REDCap just before administering vaccine. The unblinded staff will not be involved in any postvaccination procedures and are independent from the blinded team.

#### Blinding

The double-blind will be maintained from study start until the last participant has completed day 28 postchallenge follow-up visit. Unblinding at an earlier time point may occur if treatment allocation is important for a participant’s clinical management, in case of an adverse reaction. In that situation, the DSMC will guide the emergency unblinding.

No unblinded stakeholders will be involved in the assessment of study participants or in study endpoint data collection or in laboratory analysis. Unblinded members will include the statistician who generates the randomisation schedule, selected data managers and monitors, and the clinical staff responsible for vaccine preparation and administration. Blinding is implemented to minimise the risk of bias.

Both vaccines have distinct appearances. For this reason, to protect the blinding, all vaccine-related procedures will be conducted away from participants and from blinded staff. Syringes will be masked with opaque tape to reduce the risk of inadvertent unblinding.

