#### Follow-up visits

After the challenge phase, follow-up visits occur at days 28, 90 and 180 for safety monitoring and for sampling.

To confirm SPA clearance, all participants will bring three faecal samples at least 48 hours apart, at least 1 week after completing antibiotics. When all three samples are culture-negative for SPA, faecal clearance is confirmed. If any sample is positive, the participant will be retreated and followed up until clearance can be confirmed, to ensure no chronic carriage of SPA.

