### AE reporting

Participants will self-record and grade (0–4) solicited symptoms in the electronic diary for 7 days after vaccination and for 21 days after challenge. Clinicians will regularly review diaries and may contact participants if clarifications are needed. Participants will also be able to record unsolicited symptoms for 28 days from vaccination and challenge, respectively. Solicited symptoms and severity grading of AEs are described in online supplemental tables S2–S6.

AEs related to vital signs recorded in clinic and clinically significant laboratory abnormalities will be reported from vaccination to day 180, whereas SAEs will be reported from consent signing until day 180 postchallenge. Additionally, AEs related to challenge for special consideration (AERC), listed in box 2, will be monitored from challenge day through day 180 postchallenge.

Solicited symptoms will be automatically presumed to be related to the vaccine or to the challenge, depending on the diary in which they were recorded. Clinicians will complete causality assessment for all other AEs, including unsolicited symptoms, throughout the study. Events will be considered related or not related to vaccination, challenge or other interventions (eg, antibiotics).

All SAEs and AERCs will be reported to the sponsor-delegated investigator and DSMC within 24 hours of notification. SAEs related to the vaccine will be reported as SUSAR within the required regulatory timelines.

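### The double blind ends at the last participant's day 28 visit, but serious adverse events are collected and their causality judged to day 180, so late enrolees' events may be judged with allocation known

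*Protocol article*

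**What the plan says.** All references are to the protocol article.

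- **Blinding**, end of the blind: "The double-blind will be maintained from study start until the last participant has completed day 28 postchallenge follow-up visit". This is one calendar date for the whole trial. Earlier unblinding is allowed for an individual's clinical management, guided by the DSMC.
- **Blinding**, assessors: "No unblinded stakeholders will be involved in the assessment of study participants or in study endpoint data collection or in laboratory analysis". No end date is attached.
- **Study aims and objectives, Table 1**, secondary safety objective. Four outcomes are listed: "local solicited events in 7 days following vaccination systemic solicited events in 7 days following vaccination" (two outcomes), "unsolicited events in 28 days following vaccination", and "serious adverse events following vaccination throughout study participation".
- **AE reporting**: "whereas SAEs will be reported from consent signing until day 180 postchallenge". Challenge-related events of special consideration, vital-sign events and clinically significant laboratory abnormalities also run to day 180. On attribution: "Clinicians will complete causality assessment for all other AEs, including unsolicited symptoms, throughout the study". The clinician decides whether an event is related to vaccination, to challenge or to another intervention such as antibiotics.
- **Follow-up visits**: participants are seen at days 28, 90 and 180 after challenge for safety monitoring and sampling.

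**The concern.** The blind lasts as long as the primary readout needs, but one listed safety outcome runs 152 days longer. Because the blind ends on a single date, its effect depends on when a person enrolled. An early enrolee completes day 180 under the blind. A late enrolee may have the day 90 and day 180 reviews, and any SAE in between, handled by a clinician who knows the allocation.

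Deciding whether an event is due to an unlicensed vaccine, to the challenge or to antibiotics is a judgement that knowledge of allocation can sway. It also has consequences: under Safety and potential risks, and again under AE reporting, a vaccine-related SAE is reported as a SUSAR. SAEs are likely to be few, so one or two attributions could shape the late safety record.

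**Working it through.** **1. Which outcomes outlast the blind.** Day 0 is challenge and vaccination is 28 days earlier.

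| Outcome | Ends, relative to challenge | Complete by the participant's own day 28? |
|---|---|---|
| Infection (coprimary) | Day 14 | Yes |
| Anti-Vi IgG sample (coprimary) | Day 0 | Yes |
| Local and systemic solicited events | Day −21 | Yes |
| Unsolicited events | Day 0 | Yes |
| SAEs | Day 180 | No |
| Challenge-related events of special consideration (not in Table 1) | Day 180 | No |

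**2. Who is exposed.** A participant has follow-up after the blind ends if challenged less than 180 − 28 = 152 days before the last participant.

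**3. The plan's own figure.** The article gives no figure for this share. The only stated total used here is 192 (Sample size). From 85 per arm and 10% dropout, 85/0.9 = 94.4, so 95 per arm or 190 in all, which is within 2 of 192.

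**4. Longest accrual window that fits the dates.** Study design gives the first participant in March 2025 and the end of the study in September 2027. Assume the last day 180 visit falls between 1 and 30 September 2027:

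- last challenge, 180 days earlier: 5 March to 3 April 2027
- last vaccination, 28 days before that: 5 February to 6 March 2027
- blind ends, 28 days after the last challenge: 2 April to 1 May 2027
- accrual from 1–31 March 2025 to the last vaccination: 676 to 735 days

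**5. Share of participants, uniform accrual** = 152 / accrual length.

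- 152/735 = 20.7%, or 40 of 192
- 152/676 = 22.5%, or 43 of 192

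**6. Share of person-time.** Under uniform accrual an exposed participant has on average 152/2 = 76 days after the blind ends, out of 28 + 180 = 208 days from vaccination to day 180.

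- 20.7% × 76/208 = 7.6%
- 22.5% × 76/208 = 8.2%

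**7. Sensitivity to accrual.** All patterns below are assumptions.

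| Accrual pattern | Share of participants | Of 192 |
|---|---|---|
| 24 months (730 days), declining linearly to zero | (152/730)² = 4.3% | about 8 |
| 24 months, uniform | 152/730 = 20.8% | about 40 |
| 18 months, uniform | 27.7% | about 53 |
| 24 months, rising linearly from zero | 1 − (1 − 152/730)² = 37.3% | about 72 |
| 12 months, uniform | 41.6% | about 80 |

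**8. Stool clearance.** Follow-up visits requires that "all participants will bring three faecal samples at least 48 hours apart, at least 1 week after completing antibiotics". An undiagnosed participant starts a 14-day course at day 14, so the earliest samples fall at day 14 + 14 + 7 = 35, then days 37 and 39. The third comes after the blind ends only for someone challenged less than 39 − 28 = 11 days before the last participant. Under uniform accrual that is 192 × 11/735 = 2.9 to 192 × 11/540 = 3.9, about 3 to 4 people (540 days being an 18-month accrual).

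**The case against.** The strongest reply is that nothing says site clinicians or participants receive allocations at the last day 28 visit. The Blinding section keeps unblinded people away from assessment, and the unblinded roles it names do not include assessing clinicians. Who learns allocation, and when, is detail that an article may leave to the full protocol. This stands in part: a reader might infer that late follow-up will certainly be assessed unblinded, and the document does not support that. But the article does state when the double blind ends, and the undated sentence about assessors conflicts with that rule for the period up to day 180 without settling it.

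Three objections to scale hold:

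- **The safety objective as a whole is not exposed.** Three of its four outcomes end by challenge day. The Table 1 outcome is also the occurrence of SAEs, so biased attribution acts on the causality record and SUSAR reporting more than on the listed count.
- **Stool results add little.** Shedding and carriage are defined by culture, which does not depend on knowing the allocation, and few initial clearance samples fall after the blind ends.
- **The consequence is limited.** Each participant's day 28 is already 56 days after a single vaccination. SAEs and events of special consideration go to the DSMC within 24 hours, and phase I reported no SAEs in 60 adults.

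It can also be said that ending the blind at the last day 28 visit is a legitimate design choice. It is, but the primary readout does not require those who judge events to learn the allocation.

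**Conclusion.** The point holds in a narrow form and is minor. As written, the double blind ends before SAE and special-consideration follow-up is complete, so late enrolees' events may be attributed with allocation known while early enrolees' are attributed blind. Two statements in the Blinding section are unreconciled for that period. Efficacy, Vi non-inferiority and the short-term safety outcomes are not touched.

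The size rests on an assumed accrual pattern. Uniform accrual over the longest window that fits the dates gives about 21% of participants (about 40 of 192) and about 8% of person-time. A reader might take a fifth as a floor, but it is not one: a recruitment tail that dwindles gives about 4%, and rising or 12-month accrual gives about 40%.

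**What to change.** Amend the Blinding section to say three things:

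- At the last participant's day 28 visit, allocation is released only to the analysis team, for the primary readout, and any results circulated before the end of follow-up are at group level.
- Participants, site clinicians and those judging causality stay blinded until the last day 180 visit.
- Emergency unblinding is unchanged.

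This also reconciles the end-of-blind rule with the undated statement about assessors. If the sponsor prefers the present rule, the section should say who is unblinded after the last day 28 visit and that SAE attribution after that date is not blinded.

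The cost is a small text change and restricted circulation of individual allocations. The primary readout is not delayed. The downside is that sites and participants learn allocations up to about 5 months (152 days) later.
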